#### **14.2.11 Visit 8 (Week 12, Day 84 $\pm$ 3)**

- Vital signs: temperature, heart rate, respiratory rate, and supine blood pressure (after 5 minutes' rest)
- Blood sample collected for serum BG9924 PK concentration
- Study treatment administration
- Monitoring of AEs/SAEs (see Section 15.2)
- Monitoring of concomitant therapy

#### **14.2.12 Visits 8a, 8b, and 8c (Week 12, Days 86, 89, and 91; visit only applicable to PK sub-study)**

- Blood sample collected for serum BG9924 PK concentration
- Monitoring of AEs/SAEs (see Section 15.2)
- Monitoring of concomitant therapy

#### **14.2.13 Visit 9 (Week 14, Day 98 $\pm$ 3; primary endpoint evaluation, option to enter extension study, and early withdrawal visit [withdrawal prior to Week 14])**

- Physical examination
- Vital signs: temperature, heart rate, respiratory rate, and supine blood pressure (after 5 minutes' rest)
- ACR core set measurements (see Section 12.1 for list of measurements)

- QoL (SF-36, FACIT-F)
- Sjogrens assessments (see Section 12.1 for assessments), if applicable
- Blood samples collected for:
  - hsCRP and ESR (ESR to be performed at local laboratory)
  - RF and anti-CCP-2 antibody
  - RA Disease Markers (serum BAFF, COMP, calgranulin, and MMP3)
  - Quantitative FACS analysis, only in subjects participating in the optional PK sub-study (see Section 12.4 for list of variables)
  - Cytokine panel (see Section 12.4 for list of variables)
  - Serum BG9924 PK assay
  - Hematology (see Section 13.2 for list of variables)
  - Quantitative Ig (IgA, IgG, and IgM)
  - Blood chemistry (see Section 13.2 for list of variables)
  - INR, PT, and aPTT
  - ANA and anti-dsDNA antibody assays
  - Serum anti-BG9924 antibody assay
  - Tetanus antibody titers
  - RNA Analysis
- Urinalysis (see Section 13.2 for list of variables)
- Urine pregnancy test
- ECG
- Monitoring of AEs/SAEs (see Section 15.2)
- Monitoring of concomitant therapy

Visit 9 (Week 14) evaluations will be completed for all subjects who complete the treatment period or who withdraw from the study prior to Visit 9/Week 14; this will be the last visit for subjects who choose to enter the safety extension study.

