**Statistical Analysis:**

**Efficacy Analyses**

**Primary Endpoint:**

The proportion of subjects with an ACR50 response at Week 14 (Visit 9).

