| Monitoring of adverse events                     | MONITOR AND RECORD THROUGHOUT THE STUDY AS PER INSTRUCTIONS IN SECTION 15.2 |                                       |                                                   |
| Monitoring of concomitant therapy                | MONITOR AND RECORD THROUGHOUT THE STUDY AS PER INSTRUCTIONS IN SECTION 15.2 |                                       |                                                   |

CONFIDENTIAL

The information contained herein may not be used, disclosed, or published without the written consent of Biogen Idec Inc.

Vital signs include temperature, heart rate, respiratory rate, and blood pressure. Blood pressure to be performed supine after 5 minutes rest.

Measurements include: swollen and tender joint counts (66/68), subject/Investigator global assessment of disease activity, HAQ-DI, and subject's assessment of pain (VAS)

Assessments include: subject-reported dryness including VAS (ocular, vaginal, skin, and oral) and OSDI. To be conducted in subjects with Sjogrens syndrome only.

ESR to be performed at local laboratory.

RA disease markers include: serum BAFF, COMP, calgranulin, and MMP3.

**Only to be taken from subjects participating in the optional PK sub-study.**

PPD test to be read 48-72 hours after planting.

Not required if performed within 3 months prior to Day 0 and was without clinically significant abnormality. However, if PPD induration is  $\geq 5$  mm, but  $< 10$  mm (size of raised bump, not redness), a chest X-ray is required, regardless of when the last X-ray was taken.

Only to be taken from subjects with positive ANA/anti-dsDNA at Week 14.

a**Visit only applicable to subjects participating in the optional PK sub-study. Subjects will sign a separate informed consent form.**

bOption to enter safety data extension study. If subject withdraws from the study prior to Visit 9/Week 14, all Week 14 assessments should be completed at the withdrawal visit.

cIf subject withdraws from the study during the post-treatment period, Week 26 assessments should be completed at the withdrawal visit.

---

CONFIDENTIAL

The information contained herein may not be used, disclosed, or published without the written consent of  
Biogen Idec Inc.

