#### **11.4.1 Allowed Concomitant DMARD Therapy**

All subjects must be receiving MTX in the dose range  $\geq 10$  mg/week to  $\leq 25$  mg/week at Day 0, and the dose must have been stable for at least 4 weeks prior to Day 0. The dose of MTX must remain stable through to Week 14 (primary endpoint analysis), and be recorded in the CRF according to the CRF instructions.

It is possible that certain AEs that are commonly associated with MTX treatment may occur. Therefore, in order to minimize MTX toxicity, all subjects will receive folate or equivalent at a stable dose of  $\geq 5$  mg/week. This can either be as single dose given

weekly or as a divided weekly dose. It is the Investigator's decision as to which dosing regimen is used.

Concomitant use of corticosteroids for the treatment of RA is permitted if the dose is stable for at least 4 weeks prior to Day 0 and remains consistent through to Week 14. The dose must not exceed 10 mg/kg of prednisone or equivalent. No corticosteroid administration by the intra-articular route is permitted during the study.

Concomitant use of NSAIDs is permitted if the dose is stable for at least 2 weeks prior to Day 0 and remains consistent through to Week 14.

Subjects are to remain on their current stable dose of other DMARDs (hydroxychloroquine sulfate or sulfasalazine [or equivalents], or any other DMARDs unless explicitly disallowed in Section 11.4.2) through to Week 14. Doses must have been stable for 4 weeks prior to Day 0.

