#### **11.4.2 Disallowed Concomitant Therapy**

At no time during study participation may subjects receive treatment with:

- anti-TNF therapy (e.g., etanercept, infliximab, or adalimumab) or any other biologics (e.g., abatacept or rituximab),
- prosorba column,
- cyclosporin A,
- leflunomide,
- azathioprine,
- 6-MP,
- any other investigational drug or approved therapy for investigational use, or
- live or live attenuated vaccines (subjects may receive flu vaccines)

Subjects should be instructed not to start taking any new medications or therapies, including non-prescribed drugs, unless they have received permission from the Investigator.

From the start of study treatment through to Week 14, the following will be considered a rescue intervention and the subject will be considered a treatment failure:

- If the dose of any protocol-allowed concomitant DMARD therapy (including MTX) needs to be increased or
- If the administration of any new protocol-allowed or disallowed DMARD therapy is needed for the medical management of the subject.

However, it is important to note that the dose of protocol-allowed DMARD therapy can be decreased when clinically indicated for managing associated toxicity, and the subject will not be considered a treatment failure.

Any medication and any non-drug therapy or procedure used from signing of the Informed Consent Form (ICF) until the completion of the study must be recorded in the subject's CRF, according to the instructions for CRF completion. AEs related to administration of these therapies or procedures must be documented on the appropriate CRF.

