## **16.2 Criteria for the Endpoints**

All statistical tests will be 2-sided with a type I error rate of 5%. Formal statistical comparisons for efficacy endpoints will be made between each BG9924 dose group versus placebo. No adjustments will be made for multiple comparisons.

Subjects with missing efficacy measurements at the visit being analyzed will be considered treatment failures for that visit. Subjects who require rescue interventions (Section 11.4) will be considered a non-responder for all analysis time points subsequent to usage of the rescue medication. Missing values for continuous endpoint values will be replaced using last observation carried forward (LOCF).

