### **16.4 Sample Size Considerations**

A total of 380 subjects will be randomized at a ratio of 2:2:2:2:1:1 providing 76 subjects per treatment group for every other week dosing and 38 subjects per treatment group for monthly dosing. Assuming 15% dropout, a Type I error rate of 5%, Week 14 ACR50

CONFIDENTIAL

The information contained herein may not be used, disclosed, or published without the written consent of  
Biogen Idec Inc.

responses of a single BG9924 treatment group (42%) and placebo (15%), there is 90% power for a comparison of an every other week BG9924 treatment group versus placebo and 74% power for a comparison of a monthly BG9924 treatment group versus placebo by using Fisher's exact test.

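### The protocol does not settle whether an early-withdrawal assessment, or a response after a steroid increase or joint injection, counts as a Week 14 ACR50 response

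*Protocol*

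**What the plan says.** **Endpoint.** The Synopsis defines the primary endpoint by week and by visit label together: "The proportion of subjects with an ACR50 response at Week 14 (Visit 9").

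**Early withdrawal.** Footnote b to the activities table in Section 4 says: "If subject withdraws from the study prior to Visit 9/Week 14, all Week 14 assessments should be completed at the withdrawal visit". Section 11.2.2 encourages early leavers to complete the Visit 9/Week 14 tests and calls these the primary endpoint evaluation. The title of Section 14.2.13 gives Visit 9 three roles (primary endpoint evaluation, entry point to the extension, early-withdrawal visit) and a date of Day 98 ± 3. Its closing text says: "Visit 9 (Week 14) evaluations will be completed for all subjects who complete the treatment period or who withdraw from the study"; the withdrawals meant are those that come earlier than this visit.

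**Scoring.** Section 16.2 makes a subject a failure at a visit when efficacy measurements are missing at that visit, and a non-responder after a rescue intervention, for which it points to Section 11.4. It does not make withdrawal a failure in itself.

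**Background therapy.** Section 11.4 says doses of allowed concomitant therapy should not be increased. Section 11.4.1 asks for a consistent corticosteroid dose to Week 14 and adds: "No corticosteroid administration by the intra-articular route is permitted during the study". The only list of rescue interventions is in Section 11.4.2. It has two items: "If the dose of any protocol-allowed concomitant DMARD therapy (including MTX) needs to be increased or" the start of a new DMARD. Dose decreases for toxicity are expressly not failures.

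**The concern.** The non-responder rule depends on two switches, missing data and rescue, and each is loosely wired to the rest of the protocol.

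(a) If the analysis picks up records by visit label, an exit assessment sits under Visit 9, is not missing, and can be scored as a Week 14 response although the subject left weeks earlier. If the analysis goes by date, the same subject is a failure. Two analysts following the protocol could score the same person differently on the primary endpoint.

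(b) A steroid increase or a joint injection can improve joint counts and pain, which are ACR components. The protocol does not allow either up to Week 14, yet the failure list does not name them. A response obtained with their help can therefore be kept. This is a matter of confounded response, not of short treatment, and is separate from (a).

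If the choices are left until data are visible, the primary result could depend on them.

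**Working it through.** **Inputs (Section 16.4).** 76 subjects in placebo and in each every-other-week arm, 38 in each monthly arm, Fisher's exact test. "Assuming 15% dropout, a Type I error rate of 5%, Week 14 ACR50" "responses of a single BG9924 treatment group (42%) and placebo (15%), there is 90% power" for an every-other-week arm, and 74% for a monthly arm. Section 16.2 sets two-sided 5% tests.

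**Step 1: reproduce the plan's power.** Exact enumeration of both binomials, counting a win when the one-sided Fisher p-value is at most 0.025.
- Dropouts removed: 76 × 0.85 = 64.6, taken as 64; 38 × 0.85 = 32.3, taken as 32. At 42% v 15%, 64 v 64 gives 90.6% and 32 v 64 gives 74.9%.
- Dropouts kept as non-responders: 0.85 × 42% = 35.7% and 0.85 × 15% = 12.75%. Then 76 v 76 gives 89.4% and 38 v 76 gives 73.9%.

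Both routes agree with the stated 90% and 74%. The sample size is not in question.

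**Step 2: how many subjects are exposed to (a).** 0.15 × 76 = 11.4 per large arm; 0.15 × 38 = 5.7 per monthly arm.

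**Step 3: how far the reading moves the endpoint.** Let f be the share of dropouts assessed at exit and r their response rate relative to completers, the same in both arms. Neither is in the protocol, so both are assumptions. Under the label reading, response = p × (0.85 + 0.15 × f × r), with p = 42% or 15%.

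| f × r | Active | Placebo | Difference (points) | Power, 76 v 76 |
|---|---|---|---|---|
| 0 (date reading) | 35.7% | 12.75% | 23.0 | 89.4% |
| 0.25 | 37.3% | 13.3% | 24.0 | 91.2% |
| 0.5 | 38.9% | 13.9% | 25.0 | 92.7% |
| 1 | 42.0% | 15.0% | 27.0 | 95.2% |

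At f × r = 1 the label reading adds 11.4 × 0.42 = 4.8 responders in an active arm and 11.4 × 0.15 = 1.7 in placebo.

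**Step 4: false-positive rate.** Suppose completers respond at 15% in both arms and every dropout is assessed at exit.
- Exit response also 15% in both arms: the chance of a false win for active is 2.6% by an uncorrected z-test, or 1.5% by Fisher. That is no inflation.
- Exit response 30% active and 10% placebo: overall 0.85 × 15% + 0.15 × 30% = 17.25% v 0.85 × 15% + 0.15 × 10% = 14.25%. The chance becomes 7.4% (z) or 4.7% (Fisher), against 2.5% and 1.5% when all dropouts are non-responders. If only half of the dropouts are assessed, Fisher gives 2.8%.

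Inflation therefore needs a difference between arms in exit response.

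**Step 5: part (b), passages side by side.**
- Section 11.4: no increase in allowed concomitant therapy.
- Section 11.4.1: consistent steroid dose to Week 14; no intra-articular steroid.
- Section 11.4.2: failure means a DMARD increase or a new DMARD.
- Section 16.2: non-response follows rescue as defined in 11.4.

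Steroids appear under the 11.4.1 heading on allowed DMARD therapy, which could bring an oral steroid increase within the first failure item. Section 5.1 describes corticosteroids and DMARDs as different classes, which points the other way. For an injection, the protocol states a prohibition but no scoring consequence. No passage gives a rate of steroid increase or injection, so there is nothing to compute from.

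**The case against.** The strongest reply to (a) is that the date governs. Visit 9 is Day 98 ± 3, footnote b speaks of the withdrawal visit, and the sentence in 14.2.13 describes people who leave before Visit 9. A subject leaving at Week 5 (Day 35) is 60 days short of the window's opening at Day 95 and would be missing, hence a failure. Mapping exit visits to analysis windows is also ordinary SAP content. This stands in part: a reader might infer that the missing-data rule can never reach an early leaver, and the documents do not support that. But the protocol does more than leave windowing open. It labels the exit assessment as Visit 9 and as the primary endpoint evaluation, and that conflicts with its own date.

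A reader might also infer that type I error rises to 7.4%. That figure combines no true effect with exit response three times as high on active as on placebo, and uses an uncorrected test. Nothing in the protocol supports such a gap, and equal exit rates give no inflation.

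On (b), a reader might infer a large loss of power. If steroid use raised placebo alone from 15% to 18% or 20%, power would fall from 90.6% to 80.3% or 71.4% for an every-other-week arm and from 74.9% to 62.1% or 53.1% for a monthly arm. Raising both arms by the same 3 or 5 points leaves 88.5% or 87.5% for an every-other-week arm. The protocol supports neither scenario. It is fair, too, that the 11.4.1 heading lets an oral steroid increase be read as a listed failure.

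Finally, a subject who stops drug early but attends at Day 98 can still be credited. Section 11.2.1 asks such subjects to attend and 16.2 does not fail them, so that is part of the design. Nor is the endpoint a measure of 14 weeks of treatment: dosing ends at Week 12.

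**Conclusion.** The concern holds as two conflicts in how Week 14 ACR50 is scored.

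(a) The label and the date of Visit 9 give opposite scores to an early leaver who has an exit assessment. About 11 of 76 subjects per large arm are exposed at the planned dropout. The upper case, in which all are assessed and respond at completers' rates, moves the planned difference by 4 points (23.0 to 27.0) and power from 89.4% to 95.2%. With partial attendance or lower exit response the shift is smaller. Type I error is affected only if exit response differs by arm.

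(b) A response after a steroid increase or an intra-articular injection can be kept, because the failure list is silent on injections and unclear on oral steroid increases. The size is unknown, and the direction depends on which arm uses more.

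Neither point challenges the sample size. Both should be settled before unblinding.

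**What to change.** **(a)** In Section 16.2, state that Week 14 ACR50 is taken only from assessments inside the Week 14 window by actual date, and that a withdrawal assessment made earlier is scored as non-response. Give early withdrawal its own visit label in Section 4, Section 14.2.13 and the CRF, and drop the primary-endpoint description for that occasion in 11.2.2 and 14.2.13. The same assessments can still be collected.

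**(b)** Reconcile Sections 11.4, 11.4.1, 11.4.2 and 16.2 so that they say, for the analysis, how a steroid increase and an intra-articular injection before Week 14 are scored. Leave intact the 11.4.2 exemption for toxicity-driven decreases. A blanket rule failing every departure from 11.4.1 would catch those decreases, since that section also requires methotrexate to stay stable. This concerns analysis classification only; no clinical rescue rule is proposed.

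**Cost.** Wording in these sections and one CRF visit label. Concomitant therapy is already recorded. Response rates will be slightly lower than under the label reading.

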#### **14.2.14 Visit 10 (Week 18, Day 126 ±3)**

- Vital signs: temperature, heart rate, respiratory rate, and supine blood pressure (after 5 minutes' rest)
- ACR core set measurements (see Section 12.1 for list of measurements)
- Blood sample collected for hsCRP and ESR (ESR to be performed at local laboratory)
- Monitoring of AEs/SAEs (see Section 15.2)

---

CONFIDENTIAL

The information contained herein may not be used, disclosed, or published without the written consent of  
Biogen Idec Inc.

- Monitoring of concomitant therapy

#### **14.2.15 Visit 11 (Week 22, Day 154 ±3)**

- Vital signs: temperature, heart rate, respiratory rate, and supine blood pressure (after 5 minutes' rest)
- ACR core set measurements (see Section 12.1 for list of measurements)
- Blood samples collected for:
  - hsCRP and ESR (ESR to be performed at local laboratory)
  - Serum BG9924 PK concentration
- Monitoring of AEs/SAEs (see Section 15.2)
- Monitoring of concomitant therapy

#### **14.2.16 Visit 12 (Week 26, Day 182 ±3; late withdrawal visit [withdrawal after Week 14])**

- Physical examination
- Vital signs: temperature, heart rate, respiratory rate, and supine blood pressure (after 5 minutes' rest)
- ACR core set measurements (see Section 12.1 for list of measurements)
- QoL (SF-36, FACIT-F)
- Sjogrens assessments (see Section 12.1 for assessments), if applicable
- Blood samples collected for:
  - hsCRP and ESR (ESR to be performed at local laboratory)
  - Serum BG9924 PK concentration
  - Hematology (see Section 13.2 for list of variables)
  - Quantitative Ig (IgA, IgG, and IgM)
  - Blood chemistry (see Section 13.2 for list of variables)
  - INR, PT, and aPTT
  - ANA and anti-dsDNA antibody assays (only from subjects with positive ANA/anti-dsDNA at Week 14)
  - Serum anti-BG9924 antibody assay
  - Tetanus antibody titers
- Urinalysis (see Section 13.2 for list of variables)
- Monitoring of AEs/SAEs (see Section 15.2)

- Monitoring of concomitant therapy

Visit 12 (Week 26) evaluations will be completed for all subjects who complete the treatment and post-treatment period, or who withdraw during the post-treatment period.

## **15 SAFETY DEFINITIONS, MONITORING, AND REPORTING**

Throughout the course of the study, every effort must be made to remain alert to possible AEs. If an AE occurs, the first concern should be for the safety of the subject. If necessary, appropriate medical intervention should be provided.

At the signing of the ICF, each subject must be given the names and telephone numbers of study site staff for reporting AEs and medical emergencies.

### **15.1 Definitions**

#### **15.1.1 Adverse Event**

An AE is any untoward medical occurrence in a patient or clinical investigation subject administered a pharmaceutical product and that does not necessarily have a causal relationship with this treatment. An AE can therefore be any unfavorable and unintended sign (including an abnormal laboratory finding), symptom, or disease temporally associated with the use of a medicinal (investigational) product, whether or not related to the medicinal (investigational) product.

#### **15.1.2 Serious Adverse Event**

A serious adverse event (SAE) is any untoward medical occurrence that at any dose:

- results in death
- in the view of the Investigator, places the subject at immediate risk of death (a life-threatening event); however, this does not include an event that, had it occurred in a more severe form, might have caused death
- requires inpatient hospitalization or prolongation of existing hospitalization
- results in persistent or significant disability/incapacity, or
- results in a congenital anomaly/birth defect.

An SAE may also be any other medically important event that, in the opinion of the Investigator, may jeopardize the subject or may require intervention to prevent one of the other outcomes listed in the definition above. (Examples of such medical events include allergic bronchospasm requiring intensive treatment in an emergency room or convulsions occurring at home that do not require an inpatient hospitalization.)

### 15.1.3 Suspected Unexpected Serious Adverse Reactions

Suspected Unexpected Serious Adverse Reactions (SUSARs) are SAEs that are unexpected and judged by appropriate personnel at Biogen Idec and/or its designee to be related to the investigational product administered. SUSARs will be unblinded for reporting to the appropriate authorities by appropriate personnel at Biogen Idec DSRM or its designee. However, the Investigator and personnel involved in the analysis of the study will remain blinded. Expectedness of an adverse reaction will be determined according to the Investigators' Brochure for this study.

## 15.2 Monitoring and Recording Events

Any SAE experienced by the subject from the time the subject signs the ICF until the End of Study Visit, and any non-serious AE experienced by the subject after time of first dose until the End of Study Visit (see Section 7.2), is to be recorded on the CRF, regardless of the severity of the event or its relationship to study treatment. Instructions will be provided separately in the CRF Completion Guidelines.

Any AE or SAE ongoing when the subject completes the study or discontinues from the study will be followed by the Investigator until the event has resolved, stabilized, or returned to baseline status.

All events must be assessed to determine the following:

- If the event meets the criteria for an SAE as defined in Section 15.1.2.
- The relationship of the event to study treatment as defined in Section 15.3.1.
- The severity of the event as defined in Section 15.3.2.

